### Community-level archival data

School performance will also be determined using archival data from the National Assessment Program – Literacy and Numeracy (NAPLAN) data. The NAPLAN captures data for four domains (reading, writing, language conventions and numeracy). Aggregated school-level data is publicly accessible via the My School website (https://www.myschool.edu.au/). School-level performance data and school-level attendance data are also publicly accessible from the My School website.

Community level data will also include archival data on adverse events, such as alcohol-related hospital admissions; medical visits; alcohol related treatments; and police arrests for assault and related-offences, including criminal court appearances (e.g. [17]).

### Data collection in control communities

The control communities will be observed using: (1) the longitudinal school survey with 3 waves of data (see Fig. 1, flow); (2) monitoring of underage alcohol sales and (3) and archive record assessments. See schedule of enrolment and measures in Table 1.

**Table 1 Tab1:** Schedule of enrolment, intervention and assessments

		STUDY PERIOD					
	Enrolment	Allocation	Post-allocation				Close-out
TIMEPOINT	*2016*	2017	*2017/18*	*2018/19*	*2019*	*2020*	*2020*
Cluster randomization	X						
Eligibility screen		X					
Informed consent		X					
Allocation		X					
INTERVENTIONS:							
* Brief communications in Schools*				X			
* Sales Monitoring*				X			
* Control*							
ASSESSMENTS:							
* Communities That Care Youth Survey*			X		X	X	X
* Community level archival data*			X		X	X	X

### Process evaluation: intervention implementation measures

The CTC framework specifies milestones and benchmarks. Benchmarks include development of a work plan and timeline for the collection of implementation goals and outcome data for each prevention program implemented. Community implementation plans for program (Phase 4 and 5) will stipulate how it will be effective programs will be implemented and monitored to ensure that five fidelity factors are met as follows:Adherence: all components of the effective programs are used as stipulated in manuals; critical content is not added or removed;Dosage: the required number of sessions are delivered in the correct order and over the correct time periods for each program;High quality delivery: programs are delivered by qualified, expert staff;Participant involvement: the programs are delivered so participants engage with the content in line with program logic models;Saturation or reach: The program reaches target population.

Program specific checklists, observations, registration records, participant attendance logs, evaluation surveys, and training attendance logs will be used to assess implementation fidelity.

### Random allocation

The community sampling frame was initiated by selecting all Statistical Local Areas (SLAs) with greater than 17,000 inhabitants across the Australian States of Victoria, Queensland, and Western Australia. These SLAs were stratified into quartiles of socioeconomic disadvantage based on Socio-Economic Indexes for Areas (SEIFA) [18, 19]. Thirty eligible communities were randomly selected from SEIFA quartiles to represent state distributions in advantage/disadvantage and urban and nonurban locations. Of the 30 originally sampled SLAs, two were excluded from the present study due to their prior involvement in the CTC approach (see Fig. 1). The remaining 28 SLAs were paired based on SEIFA scores, urban or nonurban locations and size. An independent statistician using a computerised random number generator, allocated one of each pair to the intervention and control group, resulting in 14 intervention and 14 control SLAs, and was blind to allocation sequence.

### Statistical analyses

Intention-to-treat analyses will be employed. To account for within-individual variation we will employ repeated measures models with split-plot in time design matrix with binary outcome and logit link. Model parameters will be estimated using generalised estimating equations (GEEs) accounting for correlation within participants with an exchangeable working correlation matrix. For continuous secondary outcomes, GEEs with a Gaussian distribution and identity link will be implemented.

To assess the impact of the intervention on primary and secondary outcomes, time by treatment interactions will be examined in a model that includes the fixed categorical effects of assessment time, group indicator and treatment by group interaction. Trend effects due to staggered rollout of the intervention will be assed using models with a fixed effect categorical factor for year of treatment.

Clustering effects for schools and communities will be evaluated by calculating ICC and, if necessary, a series of (generalised) linear mixed models accounting for *clustering* (within participant/class/school/community). Analysts will not be blind to the communities that have been allocated to either intervention or control.

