## Background

Community-led interventions that systematically and strategically implement evidence-based programs have been shown to be effective in producing population-level behaviour change, including reduced alcohol and drug use. Australian guidelines recommend that adolescents should not consume alcohol before they are 18 years but 44% do, with 34% reporting use in the last 30 days [1]. Community interventions such as the “Communities That Care” prevention framework have the potential to reduce these adolescent alcohol consumption (CTC; [2–4]. The CTC framework can be used to mobilise community stakeholders and organise them to work strategically to prevent the development of harmful behaviour patterns. Communities are supported to utilise local data to identify priorities and then to plan the implementation of interventions that have been found to be effective in previous evaluations.

Large community trials in the United States of America (USA) reveal that CTC can increase community implementation of evidence-based prevention interventions and reduce health-risk behaviour patterns among teenagers, resulting in reductions of between 15% - 25% in the prevalence of youth problems [2, 4]. Economic evaluations also indicate that CTC is worthwhile investment. Conservative estimates suggest CTC can produce a return on investment of approximately US$10.23 for every dollar [5, 6]. Over ten years, pilot work developing CTC in Australia has facilitated recruitment and training of community coalitions to plan and implement evidence-based programs. This work has demonstrated feasibility of CTC in Australia. Pilot studies have shown the CTC approach has been successfully implemented with fidelity and has been associated with reductions in teenage alcohol and drug use in line with those achieved in the USA (i.e. 15%) [7]. This study will employ a Type II translational randomised control trial to evaluate the effectiveness of CTC in Australia.

The primary outcome will be the proportion of secondary school age adolescents who use alcohol before the Australian legal purchasing age of 18 years. Based on pilot work done in Australia and CTC trial work done in the USA, we hypothesise that: compared to control communities, participants in intervention communities will maintain at least a 15% lower rate of frequent (last 30 days) youth alcohol use throughout the secondary school age period (primary outcome).

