### Sample size

Previous data indicate the intraclass correlation coefficients (ICC) for alcohol consumption in the last 30 days at community and school levels were .01 and .05, respectively. We calculated the required sample with power 0.8, type I error 0.05 and design effects based on clustering effect (ICC) at community, school and classroom clustering ranging from 0.1 to 0.01. Recent Australian secondary school survey data [10] indicate rates of alcohol use in the past month were 22% in grade 8 (average age 14) and 48% in grade 10 (age 16) (combined average 35%). Assuming 65% of parents consent to their child participating, we will request informed consent from 5400 to recruit 3500 students in 2017 (wave 1). These cohorts will be resurveyed at two time points after the intervention is delivered. Assuming an 80% retention rate, the hypothesised 15% reduction can be detected with 2800 participants in the longitudinal analyses. The research team will work with communities and relevant stakeholders to recruit schools for the study. Primary outcome data will be collected in the school setting using the CTC youth survey.

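### Adjustment for community and school clustering is conditional on an undefined ICC check, although communities are the randomised unit, so the primary test and interval could be invalid

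*Protocol article*

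**What the plan says.** The protocol's Random allocation section pairs 28 areas and allocates one of each pair to the intervention, giving 14 communities per arm. The Participants section invites two schools per community.

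The Statistical analyses section fixes the primary model: "Model parameters will be estimated using generalised estimating equations (GEEs) accounting for correlation within participants with an exchangeable working correlation matrix". The intervention effect is read from the time-by-treatment interaction, with time as a categorical factor over three waves. Higher-level clustering comes later and conditionally: "Clustering effects for schools and communities will be evaluated by calculating ICC and, if necessary, a series of (generalised) linear mixed models", with class, school and community named as possible levels. No threshold or rule defines when these models become necessary.

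The Sample size section reports earlier ICCs for past-30-day drinking that "at community and school levels were .01 and .05, respectively", and says the calculation used "design effects based on clustering effect (ICC) at community, school and classroom clustering ranging from 0.1 to 0.01".

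**The concern.** In a community-randomised trial, the between-community variation belongs in the error term of the treatment comparison. A GEE clustered on participants treats about 2800 students as independent when only 28 units were randomised. If outcomes within a community or school are correlated, and that correlation does not cancel from the contrast being tested, the standard error is too small.

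The protocol treats clustering as known at the design stage and as optional at the analysis stage. An ICC check is also a weak safeguard: 28 communities estimate a community ICC poorly, and a small ICC still matters when each community supplies about 100 students. At stake is the validity of the primary p-value and confidence interval. The Gaussian GEE for continuous secondary outcomes is followed by the same conditional step.

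**Working it through.** **Inputs from the protocol.** 3500 recruited × 0.80 retention = 2800 analysed, as stated. 2800 / 28 communities = 100 students per community; 100 / 2 schools = 50 per school. ICCs are .01 (community) and .05 (school). Type I error is 0.05, taken as two-sided because the protocol does not say.

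**Step 1: comparison at one wave, clustering ignored.** With ρw the correlation of two students in the same school and ρb that of two students in different schools of the same community:

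DEFF = 1 + 49ρw + 50ρb; actual type I error = 2 × [1 − Φ(1.96/√DEFF)].

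| Reading of the ICCs | DEFF | √DEFF | Type I error |
|---|---|---|---|
| Community .01 only (ρw = ρb = .01) | 1 + 0.49 + 0.50 = 1.99 | 1.41 | 16.5% |
| Within-school .05 in total, ρb = .01 | 1 + 2.45 + 0.50 = 3.95 | 1.99 | 32.4% |
| Additive, ρw = .06, ρb = .01 | 1 + 2.94 + 0.50 = 4.44 | 2.11 | 35.2% |

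**Step 2: the test the protocol specifies.** In a change contrast, cluster effects that stay constant cancel. What matters is their autocorrelation between waves, r, which the protocol does not give. For a change between two waves, with community variance c, school variance s, remaining variance 1 − c − s and within-person correlation a:

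DEFF = 1 + (1 − r)[49(c + s) + 50c] / {(1 − r)(c + s) + (1 − a)(1 − c − s)}.

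Example with assumed a = 0.5 and r = 0.8, c = .01, s = .04: 1 + 0.2 × 2.95 / (0.2 × 0.05 + 0.5 × 0.95) = 1 + 0.59/0.485 = 2.22, a type I error of 18.8%. At r = 1 the DEFF is 1 and the error 5%.

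The three-wave, 2-df interaction test was also simulated: 28 communities × 2 schools × 50 students, 35% prevalence, no effect, assumed latent within-person correlation 0.6, participant-level robust variance, 1500 runs per cell.

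| Assumed r | Community .01 only | Plus school .04 | Plus school .05 |
|---|---|---|---|
| 1.0 | 5.7% | 5.1% | 5.4% |
| 0.9 | 6.1% | 14.7% | 16.5% |
| 0.8 | 10.6% | 20.1% | 24.9% |
| 0.5 | 19.2% | 43.0% | 46.3% |

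Monte Carlo 95% margins run from about ±1 point near 5% to ±2.5 points near 46%.

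**Step 3: can the ICC check be relied on?** This is a nested analysis-of-variance approximation at one wave, with c = .01. With s = .04, the expected mean squares are 0.95 + 50 × 0.04 = 2.95 for schools and 2.95 + 100 × 0.01 = 3.95 for communities, a ratio of 1.34. On 26 and 28 degrees of freedom, the community component is estimated at zero or below in about 23% of trials, and a 5% test of it is significant in about 18%. With s = .05 the ratio is 4.44/3.44 = 1.29, and the figures are about 26% and 16%. A true community ICC of .01 could thus easily be judged unnecessary to model.

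**The case against.** Four points on the other side deserve weight.

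- **The mixed models are foreseen.** Class, school and community are named as levels, and ICCs near the reported values could well trigger them. A reader might infer that the trial will be tested with clustering ignored. The text does not support that; it only permits it. This stands.
- **The single-wave error rates belong to a different contrast.** A reader might take 17–35% as the error of the primary test. It is not: the protocol tests an interaction in a cohort, where stable cluster differences cancel. At r = 1 the error is essentially nominal. The reported ICCs concern the level of drinking, and none is given for change. This stands, and it means that no single inflation figure, nor a claim that standard errors will be far too small, follows from the document. Pair matching might also lower the between-community variance, by an amount the protocol does not give.
- **Detail may sit in an analysis plan that is not shown.** This holds for the choice of small-sample correction. It does not dispose of the main point, because the protocol states the correlation structure and makes adjustment for the randomised unit conditional. No other section makes it mandatory.
- **Two side issues add nothing to the case.** Moving from a GEE to a logistic mixed model with participant effects changes a population-averaged odds ratio to a subject-specific one, but the numerical shift rests on a within-person correlation the protocol does not give. The statement "Analysts will not be blind to the communities that have been allocated to either intervention or control" is an open disclosure, not an error. Masking the analyst would be a separate recommendation.

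**Conclusion.** The concern holds in limited form. The written rule allows the primary analysis of a community-randomised trial to proceed without the randomised unit in the model, on the strength of an ICC check that has no threshold and little ability to detect a community ICC of .01. If the mixed models are not used, the primary p-value and interval could be invalid.

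The size is assumption-dependent. The interaction's type I error ranges from nominal to above 40% over cluster autocorrelations of 1 to 0.5, all of them assumed. It stays nominal only if community and school effects are almost frozen across the waves. The protocol offers no support for that: follow-up runs from 2017 to 2021, and the last wave includes participants who have left school. The single-wave figures show only why an ICC as small as .01 cannot be dismissed with 100 students per community.

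**What to change.** Delete the words *if necessary* and state that the primary analysis accounts for community and school in all cases. Choose one of the following before outcome data are seen:

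- a GEE with community as the independent cluster, a small-sample-corrected robust variance and between-community degrees of freedom; or
- a generalised linear mixed model with community, school and participant effects and a degrees-of-freedom correction, reported as marginal prevalences.

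Report the ICCs descriptively only, and do not let them select the model.

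The change is to analysis wording alone. The cost is wider intervals: for a single-wave comparison the standard error grows by a factor of 1.41 to 2.11 (√1.99 to √4.44). If the 15% reduction is read as relative (35% against 0.85 × 35% = 29.75%), power with 2800 students at one wave is about 84% with clustering ignored and 56%, 32% or 29% at DEFF 1.99, 3.95 or 4.44, before any degrees-of-freedom correction. For the interaction the loss is smaller the more stable the cluster effects are. The lost precision is not a reason to keep the conditional rule, because the narrower interval would not have been valid.

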### Participants and research eligibility

The primary hypothesis will be tested using a longitudinal school survey. Three waves of data will be collected; pre-intervention (baseline), and two waves post-intervention (see Fig. 1, Flow diagram).

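### The printed primary model omits the time-by-treatment term it is meant to test, and the corrected term needs one contrast on the scale of the 15% hypothesis

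*Protocol article*

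**What the plan says.** All references are to the protocol article.

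- **Statistical analyses.** The primary analysis uses "repeated measures models with split-plot in time design matrix with binary outcome and logit link", fitted by GEE. To judge the intervention, "time by treatment interactions will be examined". The model for this is described, in the same sentence, as "a model that includes the fixed categorical effects of assessment time, group indicator and treatment by group interaction".
- **Random allocation.** The word group denotes the randomised arm: an independent statistician "allocated one of each pair to the intervention and control group, resulting in 14 intervention and 14 control SLAs".
- **Participants and research eligibility.** There are three survey waves: "pre-intervention (baseline), and two waves post-intervention". The Fig. 1 caption adds that the last wave takes in Year 11 students and students who left school a year before.
- **Background.** Relative to control, intervention participants are expected to "maintain at least a 15% lower rate of frequent (last 30 days) youth alcohol use throughout the secondary school age period".
- **Sample size.** The calculation was done "with power 0.8, type I error 0.05", and concludes: "Assuming an 80% retention rate, the hypothesised 15% reduction can be detected with 2800 participants in the longitudinal analyses".

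**The concern.** There are two problems, of different weight.

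First, the list of model terms does not contain the term that the same sentence proposes to examine. Treatment and group are one factor here, so their interaction carries no information beyond the group indicator. Fitted literally, the model would have no term for an effect that differs between baseline and follow-up.

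Second, once the term is corrected, its coefficients are on a different footing from the hypothesis. Each is a ratio of odds ratios for change since baseline, one per follow-up wave. The hypothesis concerns the level of a rate, compared with control, over the school-age period. The article does not say which wave or combination of waves decides, or how a logit interaction is to be turned into a percentage. Part of the last wave also lies outside the period that the hypothesis covers. The section says that analysts will know the allocation, so a choice of contrast left open until the data are in is a real weakness.

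**Working it through.** **1. The stated figure.** 3500 × 0.80 = 2800 reproduces the attrition step. The Sample size section gives no formula, so it does not show whether the calculation was for a level at follow-up or for a change. Nothing below depends on it.

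**2. Are the printed terms estimable?** Two arms by three waves give six cells.

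| Terms (plus intercept) | Columns | Rank |
|---|---|---|
| time, group | 4 | 4 |
| time, group, treatment × group (treatment = group) | 5 | 4 |
| time, group, time × group | 6 | 6 |

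The printed interaction adds no rank. Time by group is fully estimable.

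**3. Rate scale against logit scale.** OR = [0.85p/(1 − 0.85p)] / [p/(1 − p)], at the prevalences in the Sample size section:

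- p = 0.22: (0.187/0.813)/(0.22/0.78) = 0.82
- p = 0.35: (0.2975/0.7025)/(0.35/0.65) = 0.79
- p = 0.48: (0.408/0.592)/(0.48/0.52) = 0.75

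One relative reduction therefore corresponds to several odds ratios. Conversely, holding the odds ratio at its 35% value gives reductions of 17.5%, 15.0% and 12.4% at the three prevalences.

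**4. Change against level.** Suppose follow-up is 48% v 40.8%, exactly 15% lower (OR 0.747). The interaction divides this by the baseline odds ratio. The baselines are illustrative, control v intervention:

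- 35% v 35%: 0.747/1 = 0.747
- 35% v 29.75%: 0.747/0.786 = 0.949
- 35% v 38%: 0.747/1.138 = 0.656

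The same follow-up result gives quite different interactions if the arms differ at baseline by chance, which is plausible with 14 communities per arm.

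**5. Degrees of freedom.** Three categorical waves and two arms give (3 − 1)(2 − 1) = 2. For 80% power at two-sided 0.05 on 1 df (sidedness is not stated), the noncentrality is (1.960 + 0.842)² = 7.85. The same noncentrality against the 2-df critical value of 5.99 gives power 0.709.

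**6. What baseline adjustment buys.** The protocol gives ICCs of 0.01 (community) and 0.05 (school), 28 communities, two schools each, and 2800 students, so 100 per community and 50 per school. I read the school ICC as including the community part. Assumed, and not in the protocol: within-person correlation ρ = 0.4 and cluster autocorrelation r of 0.5 to 0.9. In units of one student's variance over the number per arm, the components are community 0.01 × 100 = 1, school 0.04 × 50 = 2 and individual 0.95, a total of 3.95. For one follow-up wave:

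- Difference in differences: 2[3(1 − r) + 0.95(1 − ρ)]
- Own baseline only, slope b = 0.4: 3(1 − 2br + b²) + 0.95(1 − 2bρ + b²)
- Own baseline plus community mean: 3.95(1 − β²), with β = (3r + 0.95ρ)/3.95

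| r | Difference in differences | Own baseline only (ratio) | Own + community mean (ratio) |
|---|---|---|---|
| 0.5 | 4.14 | 3.08 (0.74) | 3.06 (0.74) |
| 0.8 | 2.34 | 2.36 (1.01) | 1.99 (0.85) |
| 0.9 | 1.74 | 2.12 (1.22) | 1.55 (0.89) |

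Adding the cluster mean lowers the variance by about 15% at r = 0.8 and 26% at r = 0.5. The student's own baseline alone gives essentially nothing at 0.8 and does worse at 0.9.

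**The case against.** The strongest reply is that the sentence itself names the time-by-treatment interaction, so a competent analyst would fit time by group and ignore the printed list. That is probably so, and the first problem should be weighed as a drafting error. The term could also be rescued by reading treatment as exposure status that switches on after delivery. The article defines no such variable; its year-of-treatment factor belongs to separate models for staggered rollout.

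Next, the corrected model is saturated in arm by wave, so prevalences can be recovered from it, and naming the primary contrast is commonly left to a statistical analysis plan, which is not at hand. This stands to the extent that a missing contrast is not in itself an error. What remains is that the article sets out a model and a hypothesis that do not match in scale, in level against change, or in period.

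A reader might go further on four points, none of which the document supports.

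- *The p-value would not test the hypothesis.* With randomised arms, an interaction of zero on the logit scale is the null of no effect, so the test is valid.
- *The hypothesis is a constant 15% reduction that the model cannot represent.* The Background says at least 15%, not constant, and categorical time allows each wave its own effect.
- *A joint 2-df test is planned, so power falls to 71%.* The article says only that interactions will be examined. The figure is conditional on that reading.
- *The sample size was built on a prevalence difference and not on a change.* No formula is given that would show either.

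**Conclusion.** The point holds in a limited form. As printed, the primary model contains an aliased term and lacks the one it is meant to test; this is wrong on the page, very likely by a slip, and should be corrected. The corrected interaction is a sound test of no effect, but it is poorly matched to a hypothesis about a lower rate during the school-age years. The mismatch concerns the estimand and its reporting and does not make the analysis unusable.

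On size: the scale effect (odds ratios of 0.82 to 0.75 for the same 15%) follows from the protocol's own prevalences. The drop from 80% to about 71% power applies only if a joint test is intended. The variance saving of about 15% to 26% rests on assumed correlations and on adjusting for the cluster mean as well as the student's own baseline. It supports the recommendation, but the case does not depend on it.

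**What to change.** - Replace the treatment-by-group term with time by group.
- Make the primary test a single 1-df intervention-control contrast, averaged over the post-baseline surveys of school-age students, adjusted for grade and for baseline 30-day alcohol use at both the student and the cluster-mean level.
- Report that contrast as a prevalence ratio and a prevalence difference, by marginal standardisation from the logit model, so that it can be set against 15%.
- Keep wave-specific effects, including the post-school responses, as secondary.

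The cost is a change of wording. The baseline responses are already collected and no new data are needed. The downsides are that post-school responses leave the primary contrast, and that the cluster-mean covariate uses one of the limited between-community degrees of freedom.

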**Fig. 1 Fig1:**
[figure not shown]
Flow chart estimating the progress of communities, schools and participants through trial. Trial registration: ACTRN12616001276448. *Wave 1 will be with either year 8 & 10, or Year 9 and 11, depending on speed in which communities work through the CTC phases, and the ease in which ethics is approved in the relevant school jurisdictions, and thus when the subsequent collection of survey data can occur. Final wave will be with year 11 students and 1 year post school. ** Approximate estimate of sample size of longitudinal cohort after 80% retention rate

Two secondary schools from each of the 28 communities will be invited to participate. Informed consent of school leaders will be required for school participation and if a school declines a nearby school will be approached. The survey will include items that assess alcohol use, and other related-behaviours as well as risk and protective factors (see measures below).

Students in the participating schools will be invited to complete the survey if they satisfy the following inclusion criteria:Are in the relevant (either Year 8 or 10) secondary school classroom grades (average age Grade 8 = 14 years; Grade 10 = 16 years);Have signed informed consent from their parents; andHave provided individual assent.

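### The primary model pools two school-grade cohorts with drinking rates of 22% and 48% without a grade term, so a difference between arms in loss of the older cohort, or in enrolment grade, would shift the last-wave treatment estimate

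*Protocol article*

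**What the plan says.** **Model.** The Statistical analyses section plans a logit GEE "accounting for correlation within participants with an exchangeable working correlation matrix". In it "time by treatment interactions will be examined", using "a model that includes the fixed categorical effects of assessment time, group indicator and treatment by group interaction". The last term names the same factor twice; from the preceding clause, time by treatment must be meant. Year of treatment enters only separate trend models. Enrolment grade is listed in neither.

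**Cohorts.** The Sample size section gives past-month drinking as "22% in grade 8 (average age 14) and 48% in grade 10 (age 16) (combined average 35"%) and assumes one overall retention of 80%, not split by cohort or arm. It also says the primary outcome is collected at school. The Fig. 1 legend states "Final wave will be with year 11 students and 1 year post school". The same legend allows wave 1 to take years 8 and 10 or years 9 and 11, depending partly on how fast communities move through the CTC phases.

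**Elsewhere.** Age appears under Secondary outcome analyses as a subgroup factor, if sample size allows. The Sensitivity analysis section states a missing-at-random assumption for the primary analyses and describes imputation, without naming the imputation variables.

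**The concern.** Grade is the strongest predictor of drinking for which the article gives figures, and it is known for everyone at enrolment. It is also a likely predictor of dropout, because the older cohort is out of school at the last wave while collection is described as school-based.

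An unweighted GEE is in general protected only against dropout that depends on covariates in the model. Loss that depends jointly on cohort and arm is not covered by time, group and their interaction. The pooled last-wave rate in each arm then depends on how many of each cohort that arm kept. The arm that loses more older students appears to drink less. If that is the intervention arm, the estimate flatters CTC; if it is the control arm, a real effect is partly hidden.

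The legend opens a second route. The CTC phases are described for intervention communities, so a wave 1 grade that depends on their pace could differ between arms.

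**Working it through.** **Inputs from the article:** 22% and 48%; a 15% reduction ("at least a 15% lower rate of frequent (last 30 days) youth alcohol use"), read as relative; exchangeable GEE with logit link; three waves; 1:1 allocation; 80% retention.

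**Assumptions (not in the article):** equal cohort sizes, as the simple mean implies; younger-cohort retention at wave 3 of 80% in both arms; older-cohort retention by arm of 80 v 70, 80 v 60 or 70 v 50%; latent within-person correlation .3 or .6; three sets of later-wave rates; dropout independent of the outcome given cohort and arm.

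**1. Planning figures.** (22 + 48)/2 = 35%, as stated. A relative 15% reduction gives 35 × .85 = 29.75%. Log odds ratio: ln(.35/.65) − ln(.2975/.7025) = −.619 + .859 = **.240**. The article does not print this value.

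**2. Mechanism by hand.** Ignore within-person correlation, assume no effect, and let the 22/48 gap persist. The wave 3 rate in an arm is (r_y × .22 + r_o × .48)/(r_y + r_o), where r_y and r_o are younger- and older-cohort retention.

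- r_o = .80: .560/1.60 = .3500, logit −.6190
- r_o = .70: .512/1.50 = .3413, logit −.6574
- r_o = .60: .464/1.40 = .3314, logit −.7017
- r_o = .50: .416/1.30 = .3200, logit −.7538

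The false interactions are −.038 (80 v 70), −.083 (80 v 60) and −.096 (70 v 50), or 16%, 34% and 40% of .240. With equal r_o in both arms the two rates are identical and the shift is zero.

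**3. The planned exchangeable GEE.** Within-person correlation recovers part of the lost information. The large-sample limits under no effect, for no grade term, are below. A negative shift favours the arm with the greater older-cohort loss.

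| Wave 3 rates, younger/older | Shift, correlation .3 (80v70; 80v60; 70v50) | Shift, correlation .6 | Share of .240 |
|---|---|---|---|
| 22/48 (gap persists) | −.0283; −.0554; −.0643 | −.0207; −.0381; −.0443 | 9 to 27% |
| 48/70 | −.0211; −.0403; −.0458 | −.0141; −.0247; −.0279 | 6 to 19% |
| 65/75 (converging) | −.0075; −.0132; −.0149 | −.0005; +.0017; +.0021 | −1 to 6% |

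A 15% relative reduction from the higher pooled rates is a larger log odds ratio: .358 at 59% and .463 at 70%. Against those, the last two rows are 4 to 13% and about 0 to 3%.

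**4. What removes it.** Grade plus grade-by-wave gives a shift of zero in every scenario. A grade main effect alone does so only if the cohort gap is constant. Otherwise it leaves a shift in the opposite direction of 1 to 8% of the scenario's effect.

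**5. Precision.** For one cross-sectional comparison, grade lowers the individual-level variance from .35 × .65 = .2275 to (.22 × .78 + .48 × .52)/2 = .2106, a fall of 7.4%. For the planned interaction, squared z relative to the model without grade is .99 to 1.03 with a main effect and .96 to .99 with grade-by-wave. There is essentially no gain.

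**6. Enrolment grade differing by arm.** The article gives no rates for years 9 and 11, so this route is not sized. A stable log-odds difference would cancel from the interaction. A shift arises where grades follow different paths over the waves.

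**The case against.** **Unequal loss alone does no harm.** A reader might infer that heavier loss of school leavers biases the comparison by itself. It does not: equal loss in both arms gives zero shift under no effect. A difference between arms is needed, and the article neither states nor assumes one. It remains a plausible risk, because intervention communities have a lead agency, grants and a community relations officer, and control communities receive no intervention.

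**Precision.** It is tempting to add that leaving grade out costs power. That would hold for a follow-up-only comparison, but the article plans a time-by-treatment contrast, in which a stable cohort difference largely cancels. Calculations of inflated standard errors also need an assumed spread of grade mix across communities, which the article does not give.

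**The model list may not be complete.** The listed terms need not be exhaustive, covariates may sit in an analysis plan that is not shown, and the imputation could already carry grade. This limits the point to the model as written. The article does name its model terms, and the imputation is described under sensitivity analysis, so nothing shown repairs the primary estimate.

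**Size.** Convergence of the cohorts with age makes the shift negligible. With the gap persisting and correlation .6, the interaction's standard error at 2800 is .085 without clustering. The largest shift there is .0443/.085, about half a standard error, and less once clustering is counted.

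**Estimand.** Whether post-school observations belong in a hypothesis about the secondary school years is a prior question that a grade term does not settle.

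**Conclusion.** The point holds as a conditional weakness of the model as written. The listed terms omit a strong, already recorded predictor of outcome that probably also predicts dropout. This leaves the last-wave interaction open to a shift of about 0 to 27% of the derived log odds ratio of .24 under assumed older-cohort retention gaps of 10 to 20 points between arms. The upper end needs both the largest assumed loss and a 22/48 gap that does not narrow; with convergence the shift is close to zero, and with equal loss by arm it is zero. Retention by cohort and arm, its spread over waves, later-wave rates and within-person correlation are all assumptions. The article supports neither a claim that differential loss is expected nor a claim that the planned test loses precision. Importance is minor to moderate; the case for acting is that the remedy costs almost nothing.

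**What to change.** - Add enrolment grade and grade-by-wave as fixed effects to the primary and secondary models. A grade main effect alone is not enough.
- Include enrolment grade in the imputation model.
- Report arm proportions at each wave standardised to a common cohort mix, so that the population-rate contrast in the hypothesis is kept.
- Correct the interaction term to time by treatment in the same sentence.

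**Cost.** Grade is already collected. With two grades and three waves the addition is one main effect and two interaction terms, so three parameters; slightly more if years 9 and 11 are also enrolled. The model odds ratio becomes conditional on cohort, which is why the standardised proportions are needed.

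**Limit.** Grade-by-wave removes the shift under no effect. If the treatment effect itself differs by cohort, dropout that depends on arm can still change the pooled effect.
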